### Intervention

To encourage behavioral changes in heavy lifting tendencies among pregnant women, the study midwives will deliver the proposed 3-component liftless intervention with the assumption that increasing knowledge will promote behavioral changes even in the face of obstacles [32].

#### Component 1: Health Education

In this component, midwives will deliver health education based on the clinical guidelines for occupational lifting in pregnancy by MacDonald et al [24]. Topics will include possible implications of heavy lifting during pregnancy, avoiding lifting any object that weighs >10 kg, avoiding lifting items over shoulder height, dividing bigger objects into smaller portions before lifting, avoiding one-handed lifting, and avoiding lifting or lowering objects below the knee. Three boosters of this component will be given, and in addition, participants will be asked to invite their spouses or significant others to attend the next session. The aim is to solicit their support throughout gestation to boost compliance with the intervention. The duration for each session will be between 60 and 90 minutes.

At the end of the session, participants will be given a lifting or carrying diary to record their daily lifting exposure. Those who cannot read or write will be provided with an alternative means, such as making ticks on a paper or asking a relative to record the information, depending on the preferred option of the participant. The diary will be checked and the contents recorded at every session. The booklet will also contain the contact information of the midwives for participants to call whenever necessary.

#### Component 2: Take-home Reminder Card

This component consists of simplified explanations on a reminder card mimicking the colors of a traffic light, Red (SEEK), Yellow (STOP), Green (HOW), based on a similar trial carried out by Lumley and Donohue [33] in Melbourne. This component will be delivered at the second session and will last between 30 and 60 minutes.

##### SEEK (Red)

A midwife’s assistance when you have questions or problems.A midwife’s assistance when you have severe lower abdominal pain, lower back pain, severe contractions, or vaginal bleeding or leaking of clear fluid (a more detailed explanation in a local language will be given).

##### STOP (Yellow)

Lifting heavy loads that weigh >10 kg, either at home or at work.Lifting more than once per 5 minutes after pregnancy has been confirmed until term.Lifting or lowering objects below the knee.Lifting items over shoulder height.

##### HOW (Green)

Divide objects into smaller portions before lifting.Attend the antenatal clinic and intervention sessions as scheduled.Seek help from close relatives when there is the need to lift an object weighing >10 kg.If possible, attend intervention sessions with a significant other.

#### Component 3: Shopping Voucher

The main focus of the third component will be the third trimester, as moderate preterm births (32 to <37 weeks) accounted for 84% of PTB in 2010, especially in sub-Saharan Africa [2]. This component is aimed to augment the uptake of the other components, as evidence has shown that voucher programs improve the efficiency and health of populations [25,26]. Participants will receive a shopping voucher equivalent to 40 GH₵ (about US $13 or 10€) at 6 different occasions beginning at the third session. The administration of the 6 shopping vouchers will span a period of 6 weeks from 32 to 37 weeks of gestation. The administration of the shopping voucher will begin with prearrangement of shops that sell items such as charcoal, water, and liquefied petroleum gas. Therefore, depending on the particular needs of each participant, they will receive a voucher to access the item from the preselected outlets, and the items will be delivered to participants at home.

Boosters of the first and second components will be delivered during the third and fourth sessions and will last between 30 and 60 minutes.

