There have been many successful health education and advice-oriented interventions that have improved patient outcomes [21]. In their quest to lengthen gestational age, midwives in LMIC such as Ghana advise pregnant women against strenuous physical activity. In certain conditions, the pregnant woman is admitted to a hospital throughout the gestational period to ensure complete bed rest to avert possible PTB [22]. Several occupational guidelines have been formulated by various institutions [19,23] aimed at protecting pregnant employees against physical stress in their respective countries. More recent are the provisional clinical guidelines for occupational lifting in pregnancy by MacDonald et al [24]. However, no such guidelines exist in Ghana and other LMIC. A recent systematic review revealed that no trial has investigated the usefulness of such guidelines aimed at reducing heavy lifting among pregnant women to increase gestational age [22]. The 3-component liftless intervention implemented in this trial is based on the clinical guidelines of occupational lifting in pregnancy by MacDonald et al [24] coupled with a shopping voucher. The rationale for the shopping voucher is to augment the uptake of the intervention components [25,26]. The shopping voucher will be administered during the third trimester with the intention of reducing moderate PTB, which is common in sub-Saharan Africa [2]. As no randomized controlled trial (RCT) has been conducted to ascertain the effectiveness of the proposed liftless intervention, the outcomes will be of public health importance for elucidating the effects of heavy lifting on birth outcomes (PTB and LBW). Through this study, a model for intervention to reduce physical exertion during pregnancy will be developed and its impact on reducing PTB and LBW will be ascertained. The success of the proposed stepped-wedge trial will justify the need for clinical guidelines to modify the occupational and family environment of pregnant women in LMIC. We hypothesize that a reduction in heavy lifting among pregnant women in Ghana will increase gestational age and birthweight.

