## Methods

### Study Design

We propose an open cohort stepped-wedge cluster RCT (PACTR201602001301205). In this design, eligible participants will be recruited until the expected numbers have been achieved. The design is a unidirectional cross-over study wherein all participating antenatal clinics will start with a control phase and eventually end up providing the intervention. The intervention will not be withdrawn once implementation has begun (at least not until the end of the trial). Participants will leave the trial when they deliver. Baseline measurements and information will be collected in all 10 clusters at the beginning of the trial using a 55-item data collection tool. Using random allocation, two clusters will transition into the intervention with each phase lasting 10 weeks. With the exception of clusters 1 and 2 (Figure 1) [27], the rest of the clusters will contribute data to the control more than once. Clusters 9 and 10 will contribute control data at 5 time points before the intervention is implemented. Thus, unlike a traditional cluster RCT where the intervention is administered only to those in the treatment group, every cluster in the stepped-wedge RCT will receive the intervention. The flow of the trial is shown in Figure 2 [28].

During the control phases, participants will receive routine antenatal care including physical and abdominal examination, blood pressure and weight measurement, urine testing, prescription of iron and folic acid supplementation, and tetanus injection. When a clinic enters the intervention phase, in addition to receiving routine antenatal care, participants will attend 5 extra intervention sessions at weekly intervals. During the sessions, study midwives will deliver the 3-component liftless intervention explaining and demonstrating all of the potential harmful task conditions, providing a take-home reminder card, and soliciting for a partner’s support. In addition, midwives will make phone calls, do home visits, and provide the shopping vouchers.

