**Figure 2 figure2:**
[figure not shown]
Flow of the trial (adopted from Standard Protocol Item: Recommendations for International Trials 2013).

Inclusion criteria.Inclusion criteria1. Pregnancy has been clinically confirmed.2. Pregnancy is between 12 and 16 weeks.3. Pregnancy is singleton.4. Exposed to lifting of 10 kg at home or work.5. Attending 1 of 10 antenatal clinics.6. Participant has consented to participate in the trial.

Exclusion criteria.Exclusion criteria1. Pregnancy has not been confirmed.2. Gestational age is above 16 weeks.3. Multiple pregnancies.4. Not exposed to lifting.5. Not attending any of the selected clinics.6. Refusal to participate.

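### The shopping vouchers have two start points, the third session and 32 weeks' gestation, which agree only if session 1 falls at about week 30; the session anchor should be deleted

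*Protocol article*

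**What the plan says.** All references are to the Protocol article.

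- **Component 3: Shopping Voucher** states two rules in adjacent sentences. Vouchers are received "at 6 different occasions beginning at the third session". Then: "The administration of the 6 shopping vouchers will span a period of 6 weeks from 32 to 37 weeks of gestation". The reason given is that "moderate preterm births (32 to <37 weeks) accounted for 84% of PTB in 2010".
- **Introduction** states the same aim: "The shopping voucher will be administered during the third trimester with the intention of reducing moderate PTB".
- **Study Design** ties the sessions to the clinic's switch: "When a clinic enters the intervention phase, in addition to receiving routine antenatal care", "participants will attend 5 extra intervention sessions at weekly intervals". It gives no gestational age for session 1 and no interval from enrolment.
- **Inclusion criteria** (textbox): "Pregnancy is between 12 and 16 weeks".
- **Component 1: Health Education**, on involving the spouse or another supporter: "The aim is to solicit their support throughout gestation to boost compliance with the intervention". The STOP section of the reminder card, which is handed out at session 2, limits lifting frequency from confirmation of pregnancy to term.
- **Primary outcome** classifies preterm birth in three bands, the earliest being below 28 weeks.

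**The concern.** One start point is a session number and the other is a gestational age. Because sessions are weekly, fixing either one also fixes when session 1 must occur, and enrolment in early pregnancy puts the two far apart unless session 1 is held back for months.

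Two things are at stake. A midwife who follows the session rule would give vouchers in the second trimester, away from the period they are meant to cover. A midwife who honours both rules would have to delay session 1, and with it the education, the diary and the card, to about week 30. The intervention would then start too late to influence the earliest band of the primary outcome.

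**Working it through.** **Inputs.** Enrolment at 12 to 16 weeks (inclusion criteria). Five sessions one week apart (Study Design). Six vouchers, starting at session 3 and also covering weeks 32 to 37 (Component 3). The lag L from enrolment to session 1 is not stated; I assume L = 0 and show a range up to 4 weeks.

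**The plan's own figure.** Weeks 32, 33, 34, 35, 36 and 37 make six weekly occasions. The gestational-age window is therefore consistent with six vouchers.

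**When the two start points agree.** Session k takes place at session 1 + (k − 1) weeks, so session 3 = session 1 + 2. Setting session 3 = 32 gives session 1 = 32 − 2 = week 30. That is 30 − 16 = 14 to 30 − 12 = 18 weeks after enrolment.

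**Prompt start.** Session 3 falls at (14 + L) to (18 + L) weeks, session 5 at (16 + L) to (20 + L), and the gap from session 3 to week 32 is (14 − L) to (18 − L).

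| Lag L (weeks) | Session 3 (week) | Session 5 (week) | Gap from session 3 to week 32 (weeks) |
|---|---|---|---|
| 0 | 14–18 | 16–20 | 14–18 |
| 1 | 15–19 | 17–21 | 13–17 |
| 2 | 16–20 | 18–22 | 12–16 |
| 4 | 18–22 | 20–24 | 10–14 |

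With L = 0, all sessions are over 32 − 20 = 12 to 32 − 16 = 16 weeks before the window opens. A four-week lag does not close the gap.

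**Women already enrolled when their clinic switches.** Their gestation at session 1 depends on the switch date, and again only those at about week 30 fit both rules. As an example on the late side, a woman at week 34 at session 1 has session 3 at 34 + 2 = week 36, and six weekly vouchers would run to 36 + 5 = week 41, past the stated window.

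**Delayed start for everyone.** With session 1 at week 30, sessions 3 to 5 fall at weeks 32 to 34. Only three of the six vouchers could then coincide with a session, so those for weeks 35 to 37 would be given outside sessions in any case. Any birth before 30 weeks, including the whole band below 28 weeks, would precede all sessions. An upper limit follows from the article's 84% figure: 1 − 0.84 = 0.16 of preterm births fall before 32 weeks. At the 14.5% rate used under Statistical Analysis and Sample Size, 0.145 × 0.16 = 0.0232, or about 23 per 1000 births. This assumes that the 84% split holds in this population. The shares before 30 and before 28 weeks are smaller and are not given.

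**The case against.** The two sentences do not contradict each other by themselves: both hold if session 3 is at week 32. The clash needs session 1 to come early, and no visible passage schedules it. The passages on partner support and on the reminder card point to an early start but set no session dates. The trial flow figure, where a schedule would naturally appear, is not shown, and a journal article condenses a fuller protocol. All of this stands, and it makes the 14-to-18-week gap conditional. It does not remove the point: one stated rule uses the wrong anchor unless session 1 is at about week 30, and that reading fits poorly with an outcome that includes births before 28 weeks.

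A reader might go further and infer that the vouchers will in practice be used up early. Six weekly vouchers from session 3 would end at 14 + 5 = 19 to 18 + 5 = 23 weeks, which is 9 to 13 weeks before week 32. The document does not support that as the expected course. The Introduction, the opening of Component 3 and the explicit window all place the vouchers in the third trimester, against a single phrase. Planning and Training also provides group training of the midwives for consistent delivery. It would likewise be too strong to say that clinics will resolve the wording differently, or that a later start flatly conflicts with the partner-support and card passages.

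**Conclusion.** The point holds as a minor inconsistency in the delivery rule. The two voucher start points agree only for a woman whose session 1 falls at about week 30. If sessions begin at enrolment, they are 14 to 18 weeks apart (10 to 14 weeks with a four-week lag). Keeping both by delaying session 1 would put the three components out of reach of births before 28 weeks. The size of the gap rests on weekly sessions, enrolment at 12 to 16 weeks and an early session 1; the last is suggested by the text but not fixed by it.

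The 23 per 1000 is a ceiling on births before 32 weeks. A reader might take it as an estimate of lost effect, but it is relevant only if every woman's session 1 were delayed to week 30, which the document does not say. Randomisation, outcome definitions, the model and the sample size are not touched.

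**What to change.** Under Component 3: Shopping Voucher, delete the phrase that starts the vouchers at the third session and define them by gestational age only: one per week from week 32 to week 37. This keeps the stated third-trimester purpose and the count of six.

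Put one question to the sponsor, to be checked against the trial flow figure: when does session 1 take place, first for women enrolled after their clinic has switched, and second for women already enrolled at the switch? The answer, including what applies to women past week 32 at the switch, is the sponsor's design decision.

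The cost is one deleted phrase and one clarification. The Results section says funding was still being sought, so on this document the change can be made before any delivery. Data collection and the analysis need no change.

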### Follow-up Telephone Call

As part of the intervention, research midwives will make telephone contact with participants after each intervention session to ascertain what measures they are taking to ensure compliance. Participants will be reminded to attend a session with their spouses or any significant family member days before a session.

### Home Visits

Research midwives will make 2 home visits (at the beginning and end of the study) with participants’ consent. The purpose is for midwives to objectively observe participants in their home environment to ascertain compliance and echo the content of the 3 components using a standardized observational checklist. The visits will also afford participants and their significant others an opportunity to seek clarification on any matters that they do not understand.

### Data Collection Tools and Data Management

First, a 55-item questionnaire will be used to collect sociodemographic data, baseline information on gestational age, family support, history of work activities, exposure to heavy lifting or carrying, lifting below the knee or above the shoulders, frequent bending, daily hours of standing, and repetitive movement. Second, the lifting and carrying diary will be used to assess participants’ self-reported daily frequency and weight of lifting and carrying and compliance. Third, participants’ antenatal and postnatal cards will be used to assess gestational age, birthweight, mode of delivery, and history of premature uterine contractions. The cards are usually filled out by midwives who provide antenatal care and deliver the child. Finally, the intervention session booklet will be used to record session attendance, participants’ complaints, and summary of education given. Any text data generated during home visits and telephone calls to or from the participants will also be recorded.

Data and materials obtained during the trial will be transferred and stored electronically, with a back-up on two memory sticks under the supervision of the primary researcher. The digital data will be disposed after dissemination and publication of the results.

### Statistical Analysis and Sample Size

We will compare the average proportion of all outcomes in the intervention group clusters to the control group clusters. We will test our hypothesis using a logistic regression model with a random effect for cluster and a fixed effect for each step of implementation of the intervention to adjust for possible effects of calendar time [34,35].

If there are major baseline differences between the intervention and control clusters for potential confounders, such as prolonged standing or squatting, parity, maternal age, infection, occupation, educational level, marital status, and nutritional status, we will include these as covariates in the model. Intention to treat will be the basis for the statistical analysis to ensure that all clusters (with participants) are randomized and included in the final analysis regardless of completion of the study or not [36].

For the sample size calculation, we set alpha at 0.1 and beta at 0.8. We assumed that the intervention will decrease PTB rate by 30% (ie, from 14.5% to 10.5%, with 14.5% being the current official PTB rate in Ghana). With 10 antenatal clinics, we estimated that we need 1000 participants to provide the power to detect a 30% difference in the rate of PTB between the control and intervention clusters. The individual performing the analysis will be blinded to the treatment allocation.

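### Covariate adjustment depends on an undefined major imbalance and is not committed to baseline lifting, the exposure the trial sets out to change

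*Protocol article*

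**What the plan says.** Statistical Analysis and Sample Size sets the primary model as a "logistic regression model with a random effect for cluster and a fixed effect for each step of implementation of the intervention". Individual covariates are not in it by default. They enter conditionally: "If there are major baseline differences between the intervention and control clusters for potential confounders". No threshold for *major* is given. The confounders are introduced by *such as*, so the list is illustrative: "prolonged standing or squatting, parity, maternal age, infection, occupation, educational level, marital status, and nutritional status".

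Lifting is recorded elsewhere in the plan. Under Data Collection Tools and Data Management, the 55-item questionnaire covers "exposure to heavy lifting or carrying, lifting below the knee or above the shoulders, frequent bending, daily hours of standing, and repetitive movement". On timing, Study Design says: "Baseline measurements and information will be collected in all 10 clusters at the beginning of the trial using a 55-item data collection tool". The inclusion criteria require "Exposed to lifting of 10 kg at home or work", with no upper limit, weight band or frequency.

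Under Randomization and Blinding, clinic order is randomized before the trial starts, and neither midwives nor participants are blinded. Under Study Population and Recruitment, the study midwives enrol the women over 60 weeks.

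**The concern.** The list names one physical-load item, prolonged standing or squatting, and omits the load the trial acts on. If the hypothesis is right, baseline lifting predicts preterm birth. Because eligibility sets only a 10 kg criterion, lifting can vary widely among eligible women.

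Randomizing the order of clinics does not balance the women who enrol before and after a switch. What a woman is asked to accept changes at crossover: five extra weekly sessions, some lasting 60 to 90 minutes, a daily diary, and vouchers during pregnancy rather than after delivery. Women with heavy workloads might then enrol at a different rate, and an unblinded recruiter might apply the lifting criterion differently. If lighter lifters enrol after the switch, the estimate is biased in favour of the intervention; if heavier lifters enrol, it is biased against it.

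At stake is whether part of an observed difference in preterm birth reflects who enrolled rather than what they received.

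**Working it through.** The plan gives no figure for the effect of lifting on preterm birth or for a shift in lifting between phases. There is therefore nothing to reproduce, and what follows is an illustration on assumed values.

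**1. What the model removes.** The random cluster effect largely absorbs stable differences between clinics. The fixed step effects absorb calendar trends common to all clinics. A change in the mix of women within a clinic at its own crossover coincides with the treatment term, so neither effect removes it. Only this kind of shift matters here.

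**2. Planned effect on the log-odds scale.** The rates printed under Statistical Analysis and Sample Size are 14.5% and 10.5%.
- Control odds: 0.145/0.855 = 0.1696
- Intervention odds: 0.105/0.895 = 0.1173
- Log odds ratio: ln(0.1173/0.1696) = -0.369

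**3. Bias from a shift.** To first order, bias = ln(odds ratio per SD of lifting) × shift in SD. Assumed ranges are an odds ratio of 1.3 to 1.6 and a shift of 0.2 to 0.3 SD.
- Low: ln(1.3) × 0.2 = 0.262 × 0.2 = 0.052; 0.052/0.369 = 14%
- High: ln(1.6) × 0.3 = 0.470 × 0.3 = 0.141; 0.141/0.369 = 38%

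An exact 30% reduction (10.15%) gives a log odds ratio of -0.406 and shares of 13% to 35%.

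**4. Cross-check on the risk scale, with different assumptions.** Suppose half of control enrolees are heavier lifters, the control rate is 14.5%, the intervention has no true effect, and the share of heavier lifters falls by s after crossover. With risk ratio RR for heavier versus lighter lifters, the risk in lighter lifters is r0 = 0.145/(0.5 × RR + 0.5), and the spurious reduction is r0 × s × (RR - 1).

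| RR | s = 10 points | s = 20 points |
|---|---|---|
| 1.1 | 0.14 points | 0.28 points |
| 1.3 | 0.38 | 0.76 |
| 1.5 | 0.58 | 1.16 |
| 2.0 | 0.97 | 1.93 |

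Against the planned 4.0 points this runs from 0.14/4.0 = 3% to 1.93/4.0 = 48%. With RR = 1 or s = 0 the bias is zero.

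**5. Room in the model.** With equal numbers in the two conditions, expected preterm births are 1000 × (0.145 + 0.105)/2 = 125, enough to carry one or two further terms.

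**The case against.** A reader might infer that lifting has been ruled out as a covariate, so that any shift passes directly into the effect estimate. The text does not support this. The list is open, and the rule as written would let lifting be added if a major difference were seen. Occupation, which is named, partly reflects lifting. What remains is that *major* is undefined and nothing obliges the analyst to look at lifting or adjust for it.

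A reader might also infer that weight and frequency of lifting are already recorded at baseline in every woman. The article assigns daily frequency and weight to the lifting diary. For the questionnaire it states only "exposure to heavy lifting or carrying, lifting below the knee or above the shoulders" and related items. Study Design places baseline collection at the beginning of the trial and does not spell out when later enrolees complete it, yet these are the women in whom a shift would show.

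The strongest objection is that a condensed article may leave its full covariate set to an analysis plan that is not shown. That would answer a complaint about missing detail. Here, however, the article does state its adjustment rule, and that rule depends on the data. Committing to a baseline value the trial already intends to collect is a better method at almost no cost.

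Finally, the magnitude is assumed, and the Abstract and Introduction themselves describe the evidence on lifting as inconclusive. That stands: the figures show what could happen, not what is expected.

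**Conclusion.** The point holds as an inexpensive improvement, not as a demonstrated bias. The plan adjusts only on an undefined trigger and does not commit to the baseline variable most closely tied to entry, intervention and hypothesised outcome. Enrolment by unblinded midwives after randomization makes a within-clinic shift at crossover possible, and the stated model would not remove it.

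On the assumed odds ratios and shifts, the bias is 0.05 to 0.14 in log odds, or 14% to 38% of the planned effect. The risk-scale check gives 3% to 48%. Neither set of assumptions has a source in the article. The direction depends on who enrols, and the true value could be near zero.

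**What to change.** State in the analysis section that baseline lifting exposure, from the 55-item questionnaire, enters the primary model as a fixed covariate whatever imbalance is observed. State also that each woman completes the questionnaire at her own enrolment, before any intervention session. Tabulate baseline lifting by clinic and by phase at enrolment, so that a shift at crossover can be seen.

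Do not take this covariate from the lifting diary. Under Component 1: Health Education, the diary is handed out at the end of a session, and it records the behaviour the intervention is meant to change. Adjusting for it could remove part of the effect under study. If weight and frequency are wanted as baseline values, first confirm that the questionnaire asks for them.

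The cost is a sentence or two and one or two model terms. Adjustment removes only the measured, self-reported part of any imbalance. Funding was still being sought when the article was written, so the change could be made before enrolment.

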## Discussion

We propose an interventional study to fill the research gap on whether heavy lifting in pregnancy has negative effects on gestational age and birthweight, particularly among women in LMIC. There is no intervention study on the effects of lifting in pregnancy on birthweight and gestational age. Similar to many other health indicators, PTB and LBW prevalence rates underscore the overwhelming health disparities and inequalities between high-income and low-income countries. Strenuous physical activity, LBW, and PTB are common occurrences in low-income countries, which lack guidelines to protect against hazardous work conditions [11]. There are inconsistencies in the existing etiological studies on the subject, thereby creating an evidence gap [22]. As a result of the inconsistencies, recommendations and all other clinical guidelines lack the necessary evidential backing for practice. This clinic-level intervention using a stepped-wedge design will thus provide a vital contribution to the existing knowledge for the prevention of PTB and LBW, especially within LMIC.

Problems anticipated in the course of this intervention may arise from participant attrition, especially among controls, due to the longer duration of the trial. We intend to reduce attrition by explaining the potential benefits of the trial in detail and providing shopping vouchers, which is the third component of the intervention, to all control participants during postnatal periods. The strengths of the trial include the prospective data collection method, the study design, and the size of the study population. The results of this trial have the potential to justify the need for policy to modify the occupational and family environment of pregnant women within Ghana and other LMIC with similar socioeconomic conditions.

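### The sample-size statement contradicts itself, and 1000 women give at most about 60% power at the stated alpha under the planned stepped-wedge model, not the implied 80%

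*Protocol article*

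**What the plan says.** The Statistical Analysis and Sample Size section of the protocol article gives the error rates: "For the sample size calculation, we set alpha at 0.1 and beta at 0.8". It does not say whether alpha is one- or two-sided.

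The assumed effect is that "the intervention will decrease PTB rate by 30% (ie, from 14.5% to 10.5"%. The section concludes that, with 10 clinics, "we estimated that we need 1000 participants to provide the power to detect a 30% difference in the rate of PTB".

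The same section plans a logistic model with a random cluster effect and a fixed effect for each step. No ICC, design effect, stepped-wedge formula or dropout allowance accompanies the figure of 1000. The Discussion nevertheless expects losses: "Problems anticipated in the course of this intervention may arise from participant attrition", particularly among controls. It also counts the size of the study population among the trial's strengths.

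**The concern.** Three items in the statement do not fit together.

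- Beta is the type II error rate, so beta 0.8 means 20% power.
- The relative reduction and the two percentages disagree.
- The total of 1000 is close to what a simple two-arm comparison would need under favourable choices, although the trial is a 10-clinic stepped wedge whose own model adjusts for time.

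The first two are reporting errors and do not themselves cause low power. The third matters more. If the trial has much less than 80% power for its primary question, a non-significant result says little about a 30% reduction in preterm birth. A reader who trusts the power statement could take it as evidence that reducing lifting does not help.

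**Working it through.** **Inputs.** From Statistical Analysis and Sample Size: alpha 0.10, 14.5% versus 10.5% (or a 30% reduction), 1000 women, 10 clinics, random cluster effect and fixed step effects. From Study Design: two clinics cross at each step, phases last 10 weeks, and the last two clinics give control data at five time points. From Study Population and Recruitment: 60 weeks in all. This gives 60/10 = 6 periods and 1000/(10 × 6) = 16.7 women per clinic-period if recruitment is even. Power 0.80 is taken as the intended target. ICC values above 0 are assumptions, because the article gives none.

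**Step 1: internal consistency.**
- 14.5 × 0.70 = 10.15, not 10.5.
- (14.5 − 10.5)/14.5 = 27.6%, not 30%.
- Taken literally, 20% power for 14.5% versus 10.5% would need only about 53 women (one-sided 0.10) or 177 (two-sided 0.10) under individual randomisation. Beta 0.8 therefore cannot be what produced 1000.

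**Step 2: trying to reproduce 1000.** For two equal, individually randomised arms,

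N = 2 × [z_α √(2p̄(1−p̄)) + z_β √(p₁(1−p₁) + p₂(1−p₂))]² / (p₁−p₂)².

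For 14.5% versus 10.5%, one-sided 0.10: 2 × [1.2816 × 0.4677 + 0.8416 × 0.4669]² / 0.0016 = 1231. The other cases follow in the same way:

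| Rates | One-sided 0.10: N for 80% | Power at 1000 | Two-sided 0.10: N for 80% | Power at 1000 |
|---|---|---|---|---|
| 14.5% vs 10.5% | 1231 | 74% | 1688 | 61% |
| 14.5% vs 10.15% | 1028 | 79% | 1410 | 67% |

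Of these four, only the one-sided 10.15% case comes near 1000. It contradicts the printed 10.5% and contains neither clustering nor period effects.

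**Step 3: the planned design with ICC 0.** The number of treated clinics over the six periods is 0, 2, 4, 6, 8, 10. Overall half of the cells are treated, so the variance of the treatment indicator is 0.5 × 0.5 = 0.25. Once period effects are fitted, only the within-period part is left: (0 + 0.16 + 0.24 + 0.24 + 0.16 + 0)/6 = 0.1333. The variance of the effect estimate therefore rises by 0.25/0.1333 = 1.875.

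The standard error of the risk difference is √[p̄(1−p̄)/(1000 × 0.1333)].
- 10.5%: p̄ = 0.125, SE = 0.0286, 0.040/0.0286 = 1.40. Power is Φ(1.40 − 1.28) = 55% one-sided and Φ(1.40 − 1.645) = 40% two-sided.
- 10.15%: p̄ = 0.12325, SE = 0.0285, 0.0435/0.0285 = 1.53. Power is 60% one-sided and 45% two-sided.

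**Step 4: adding within-clinic correlation.** This uses the generalised least squares variance (Hussey–Hughes) with fixed period effects, a random cluster effect and, in the last row, a cluster-period effect. CAC is the cluster autocorrelation. Each cell shows one-sided 0.10 / two-sided 0.10 power.

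| ICC (assumed) | 14.5% vs 10.5% | 14.5% vs 10.15% |
|---|---|---|
| 0 | 55% / 40% | 60% / 45% |
| 0.01 | 49% / 35% | 53% / 39% |
| 0.02 | 47% / 33% | 51% / 37% |
| 0.05 | 45% / 31% | 49% / 35% |
| 0.05, CAC 0.8 | 42% / 29% | 46% / 32% |

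If the final test used two-sided 0.05, power for 10.15% would be 33% at ICC 0, 28% at ICC 0.01 and 22% at ICC 0.05 with CAC 0.8. An assumed 10% attrition takes off about 2 to 3 further points at alpha 0.10.

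**Step 5: what 1000 women could detect.** At two-sided 0.10 and 80% power the detectable difference is (1.645 + 0.842) × SE. For the 10.15% rates this is 2.487 × 0.0285 = 7.1 points at ICC 0 and 2.487 × 0.0366 = 9.1 points at ICC 0.05 with CAC 0.8. Relative to 14.5% these are reductions of 49% and 63%.

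For the printed 10.5%, 80% power at ICC 0.01 to 0.05 (CAC 1) would need about 4800 to 5040 women (two-sided 0.10) or 3390 to 3660 (one-sided 0.10).

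**The case against.** The strongest reply is that a journal article condenses. It shows no ICC or design effect, but that does not prove none was used, and the sum mentions the 10 clinics. That is fair, and the omission should not be stated as fact. It does not rescue the figure, though. Printed rates, alpha 0.10 and 80% power already require more than 1000 without any clustering, the step effects in the printed model bring power to 60% or less at ICC 0, and every positive ICC tried lowers it further.

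A second reply is that the percentages are approximate. This also stands in part. They assume equal recruitment across clinics and periods, although the article says the facilities vary in size. They also place each woman in one period with one exposure status, whereas women enrol at 12 to 16 weeks and stay until delivery, so a pregnancy can span several phases. The approximation is linear on the risk-difference scale rather than logistic. The direction and rough size are secure; the exact percentages are not. Any single range also mixes sidedness and assumed effect, which is why the tables separate them.

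Third, 1000 might be read as 100 women per clinic in every period. That would give about 86% to 96% power (two-sided 0.10, 10.5%), but it means 6000 births, and the article says 1000 participants over 60 weeks.

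Finally, beta 0.8 and 10.5% may be slips of the pen, and the article sets no rule for interpreting a null result. Both are true. Correcting the slips still leaves 1000 unsupported, and the risk of misreading a null result is a judgement about readers.

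**Conclusion.** The concern holds. Beta is misstated, the 30% and the 10.5% disagree, and 1000 women do not give 80% power under the described design and model.

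At ICC 0, power at alpha 0.10 is 55% one-sided or 40% two-sided for the printed rates, and 60% or 45% for an exact 30% reduction. Over the assumed correlations it falls as low as 42% or 29%, and 46% or 32%, respectively. No setting examined exceeds 60%. The ICC 0 figures need no outside value; they rest on six periods, even recruitment and one period per woman. The lower figures also depend on the assumed ICC and autocorrelation. Because this is the power claim for the primary outcome, it should be corrected before the trial starts.

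**What to change.** 1. Replace the beta statement with power 0.80 (beta 0.20), if that is what was intended.
2. State whether alpha 0.10 is one- or two-sided, and that the final test uses the same level.
3. Make the effect size consistent: either 14.5% to 10.15% (30%), or 14.5% to 10.5% (27.6%).
4. Replace the claim about 1000 participants with the power, or the detectable difference, for the actual 10-clinic, six-period stepped wedge. Give it over a stated ICC range, with the cell-size assumption and an attrition allowance.
5. State that a non-significant result is inconclusive for a 30% reduction and that the confidence interval will be the basis for interpretation.

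The cost is protocol wording, and the declared power becomes less favourable. These corrections do not by themselves require more women. Funding was still being sought when the article was written, so the sponsor can still choose between declaring the lower power and reconsidering the size or design.
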